### Outcomes

The primary outcome of interest is the feasibility, which is determined by the following:Recruitment—ability to recruit on an average of four patients per month.Adherence—at least 80% of patients adhere to 80% of allocated treatment and protocolRetention of subject—at least 80% of patients remain followed up to 12 months.

All secondary outcomes will be ascertained during the week 4, 12, 24, 36, and 48 visits, as well as by monthly in-person or phone assessments by our study coordinator. Study participants will be encouraged to call the study coordinator anytime if they experience any adverse events. Secondary outcomes are as follows:Safety: This will be assessed by documentation of adverse events in patients treated with Ig treatment versus control. Known adverse events associated with the treatment include headache, chills, fever, weakness, nausea arthralgia, malaise, urticaria, leukopenia, tachycardia, hypotension, anaphylaxis, localized injection reactions, and thrombotic events (arterial or venous). All adverse events will be graded by the investigator using a 5-point scale (Table 1) and scored as to attributability to study treatment.Tolerability: The proportion of patients able to complete the treatment in the experimental arm during the study period versus in the control arm.Efficacy trends (this study is not powered to show significance):AECOPD outcomes will be measured by (i) percentage of patients with one or more AECOPD episode, (ii) time from randomization to the first moderate or severe AECOPD, and (iii) annualized moderate or severe AECOPD rates (number of exacerbations/12 months). AECOPD will be ascertained by monthly follow-up phone calls to detect outpatient treatment for exacerbations. AECOPD is defined as a complex of increased or new onset respiratory symptoms of more than one of cough, sputum, wheezing, dyspnea, or chest tightness, with a duration of at least 3 days requiring treatment with prescribed antibiotics and/or systemic steroids [3]. Research staff will determine if the patients have met this definition of exacerbation, or if the patient was treated with antibiotics or steroid medication for an AECOPD.Health status will be measured by the validated St. George Respiratory Questionnaire (SGRQ) and COPD Assessment Test (CAT) scores.Quality of life will be measured by the validated quality of life measurement tool, EuroQol EQ-5D-5L.FEV1 and FVC measurements will be carried out with a hand-held spirometer and recorded in liters and as a percent of their predicted value, using the NHANES III reference standards for predicted values.Health services use is defined by non-study physician visits, ED, and hospital admissions over the 12-month study period. Research staff will ascertain this by reviewing the patient’s medical record and confirming any hospital visits and cause with the patient and his/her primary care provider.Healthcare system cost: We will measure the cost of health services use and the intervention. Intervention cost includes medication, staff, and equipment cost. The data will be captured by clinical report forms, TOH warehouse database, and a cost questionnaire (Additional file 1) designed for this study, which will be collected at weeks 12, 24, 36, and 48.

**Table 1 Tab1:** Five-point grading scale of adverse events

1 = mild	Discomfort noticed but no disruption of normal daily activity
2 = moderate	Discomfort sufficient to reduce or affect daily activity
3 = severe	Inability to work or perform normal daily activity
4 = life threatening/disabling	Represents an immediate threat to life
5 = death	Related to adverse event

In order to avoid bias and inaccurate reporting, a blinded outcome adjudication committee will be formed to assess the outcomes documented by trial investigators as well as outcomes not captured by the investigators but by other healthcare professionals. There will be two independent blinded experts appointed for the outcome adjudication process. The outcome adjudication committee will assess the outcome data every 12 months until study closure.

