Participants may withdraw from the study at any time and for any reason; however, they will be encouraged to stay on their assigned study medications in the absence of illness- or treatment-related adverse events. All patients will be followed up for adverse events and outcomes for 1 year from randomization. The sponsor (OHRI), the qualified investigator, or a treating physician may withdraw the participant at their discretion or in the event of intercurrent illness, intolerance to the study treatment, adverse events, pregnancy, protocol violation, or administrative reasons. All participants discontinued due to an adverse event will be followed until the event resolves or becomes chronic or stable. Appropriate medical care will be provided until signs and symptoms have remitted or stabilized or until abnormal laboratory findings have returned to acceptable or pre-study limits.

After the study completion, patients will continue their clinical care with their primary care provider or specialist, as prior to and during the study period. Patients may elect to stay on IVIG treatment by prescription according to the judgment of the treating physician.

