### Study visits

Participant study visits are detailed in Table 2. Study visits will include a pre-treatment evaluation to obtain informed consent and demographic information as well as assess eligibility for participation. At a baseline study visit (week 0), treatment allocation and the first infusion of IVIG or normal saline will take place. Infusion of IVIG or normal saline will continue on monthly treatment visits (± 6 days). Assessment of primary and secondary outcomes will take place as indicated in Table 2. Adverse events, a review of concomitant medications, and the CAT questionnaire will be assessed on follow-up via monthly telephone calls. Note that the total study period is planned for 2 years (1-year accrual period and 1-year follow-up of each subject). All patients will be followed up until the end of the study closure or until the last recruited subject is followed for 12 months from the time of enrolment in the study.

**Table 2 Tab2:** Study visits and participant timeline

	Enrolment	Week 0	Week 4	Week 8	Week 12	Week 16	Week 20	Week 24	Week 28	Week 32	Week 36	Week 40	Week 44	Week 48	Follow-up
Written informed consent	X														
Demography	X	X													
Eligibility verification	X	X													
Allocation		X													
Complete physical exam	X														
Vital signs including Sp02	X	X	X	X	X	X	X	X	X	X	X	X	X	X	
Height	X														
Weight	X	X	X	X	X	X	X	X	X	X	X	X	X	X	
Urine pregnancy test^1^	X														
Pulmonary function test or spirometry	X	X^a^	X		X			X			X			X	
Target physical exam			X		X			X			X			X	
Immunoglobulin profiles and other hematological and biochemical tests^2^	X		X^b^		X^b^			X^b^			X^b^			X^b^	
CT chest, chest X-ray, sinus X-ray^3^	X	X													
ECG, nasopharyngeal swab, sputum culture^4^	X	X													
Medical history	X	X	X	X	X	X	X	X	X	X	X	X	X	X	X
Adverse event assessment	X	X	X	X	X	X	X	X	X	X	X	X	X	X	X
Concomitant medications	X	X	X	X	X	X	X	X	X	X	X	X	X	X	X
Infusion of Ig or normal saline		X	X	X	X	X	X	X	X	X	X	X	X	X	
EQ-5D-5L questionnaire		X	X		X			X			X			X	
SGRQ questionnaire^5^		X	X		X			X			X			X	
COST Questionnaire			X		X			X			X			X	
CAT Questionnaire		X	X	X	X	X	X	X	X	X	X	X	X	X	X
Hunch survey				X										X	X

All laboratory tests will be performed at the hospital

^1^Only women of child-bearing potential will have a pregnancy test conducted at the screening visit

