### Sample size

For feasibility, safety, and tolerability, we will aim to recruit 16 outpatients and 48 inpatients. As this is a pilot study, we will not power the study to show efficacy in exacerbation reduction. Informed by our current clinic patient volume, we estimate that we can feasibly recruit 64 patients in the 2-year study period and have chosen this as the target sample size for this pilot trial. However, if we conservatively assumed that 30% of severe COPD patients develop exacerbation episode within 12 months [10], 59 patients would be required on each arm to have 80% power to detect 20% reduction in AECOPD within 12 months. Based on our case series [25], there was an 86.2% apparent reduction in the average number of exacerbations in 1 year in patients treated with immunoglobulin. This data may be used to estimate the sample size for a future trial of similar design.

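### The primary recruitment criterion of four patients per month is not aligned with the target of 64 and the stated accrual period

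*Protocol article*

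**What the plan says.** Four statements in the protocol article bear on recruitment.

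- **Outcomes**: the first component of the primary feasibility outcome is the "ability to recruit on an average of four patients per month". The section gives no period for the average and does not connect the figure to a target.
- **Study visits**: "the total study period is planned for 2 years (1-year accrual period and 1-year follow-up of each subject". Accrual is therefore 12 of the 24 months. The same section continues follow-up to study closure or "until the last recruited subject is followed for 12 months from the time of enrolment in the study".
- **Sample size**: "we will aim to recruit 16 outpatients and 48 inpatients", a total of 64. It adds that "we estimate that we can feasibly recruit 64 patients in the 2-year study period" and takes this number as the target.
- **Interventions**: "All patients will be followed up for adverse events and outcomes for 1 year from randomization".

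No section explains how the monthly criterion was chosen or how it relates to the target of 64.

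**The concern.** A recruitment criterion in a pilot trial should tell the reader whether the planned enrolment was achievable in the planned time. That requires the rate, the accrual duration and the target to fit together, or a stated reason why they do not. Here the rate fits neither the one-year accrual in Study visits nor the two-year period in Sample size.

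This matters because feasibility is the primary outcome, and both the Background and the Discussion make the larger trial conditional on it. As the text stands, the trial could meet its recruitment criterion with a quarter of the target missing. On another reading of the same article, it could enrol every planned patient and miss the criterion. Because the averaging period is not fixed, the choice between these readings could be made after enrolment is known. Trial status says that recruitment is already under way.

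**Working it through.** **Inputs, all from the protocol article**

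- Criterion: 4 patients per month (Outcomes).
- Accrual: 12 months; total study: 24 months (Study visits).
- Target: 64 patients, made up of 16 outpatients and 48 inpatients (Sample size).
- Follow-up: 12 months per patient (Interventions, Study visits).

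**Step 1. The target itself.** 16 + 48 = 64. The stated total is reproduced.

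**Step 2. Patients at the criterion rate** (patients = monthly rate × months of accrual)

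- One-year accrual: 4 × 12 = 48. This is 64 − 48 = 16 short, and 48/64 = 75% of target.
- Accrual over two years: 4 × 24 = 96.

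Neither stated period gives 64.

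**Step 3. Rate implied by the target** (rate = patients / months of accrual)

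- One-year accrual: 64/12 = 5.33 per month. This is 5.33/4 = 1.33 times the criterion; equivalently, the criterion is 4/5.33 = 75% of the rate needed.
- Accrual over two years: 64/24 = 2.67 per month, which is 2.67/4 = 67% of the criterion.

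**Step 4. Accrual duration at which criterion and target agree**

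- 64/4 = 16 months. With 12 months of follow-up for the last patient, the study lasts 16 + 12 = 28 months. Neither duration appears in the article.
- It follows that a trial that reaches 64 passes the criterion if accrual took 16 months or less, and fails it if accrual took longer.

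**Step 5. The two periods against each other.** If recruitment runs for the full 24 months, the last patient finishes follow-up at about 24 + 12 = 36 months. Nobody enrolled after month 12 could complete 12 months of follow-up by month 24. A literal reading of Sample size therefore conflicts with Study visits even without the monthly criterion.

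| Accrual | Patients at 4 per month | Rate needed for 64 | Reaching 64 passes the criterion? | Total study |
|---|---|---|---|---|
| 12 months | 48 | 5.33 | yes | 24 months |
| 16 months | 64 | 4.00 | yes, exactly | 28 months |
| 24 months | 96 | 2.67 | no | about 36 months |

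**The case against.** The strongest reply is that four per month is a success threshold and not the planned rate. The other two feasibility criteria are minimum proportions of 80%, so reading this one as a minimum is natural. Enrolling 64 in 12 months is 5.33 per month, which clears it. Study visits defines the two-year study as one year of accrual plus one of follow-up. If Sample size uses the phrase in that sense, all 64 enter in the first year and nothing is violated. This stands: a reader might infer that the three figures are mutually exclusive, and the article does not support that. The 2.67 per month arises only if recruitment really runs through both years. That is the literal wording of Sample size, but it goes against the explicit split in Study visits.

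A threshold below the target rate is also a legitimate design choice. The weakness is that the article neither states that choice nor gives a reason for a bar at 75% of the rate the plan needs.

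A reader might further infer that missing the criterion would stop the programme or make the trial infeasible. No section states a go/no-go rule or says how the three components combine, and the analysis section plans only a descriptive account of recruitment. The observed rate stays usable whatever the bar, and no treatment comparison or safety estimate depends on it.

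Finally, 48 inpatients over 12 months is exactly 48/12 = 4 per month, and the design section mentions separate protocols for inpatients and outpatients. The criterion may have come from the inpatient part alone. That is only an inference: Outcomes applies the figure to patients without restriction.

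The averaging period might be left to a fuller document and would not be a finding by itself. It enters here only because the two periods in the article give opposite answers.

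**Conclusion.** The concern holds as a misalignment of stated figures in a primary criterion, not as a proven contradiction. With one-year accrual, the bar is passed at 48 patients, 16 below target, and reaching the target needs a rate one third above the bar. With recruitment spread over two years, a trial that reaches its full target runs at 2.67 per month, one third below the bar, and cannot complete 12-month follow-up within the stated study length.

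The first result assumes that Study visits fixes accrual at 12 months. The second assumes the literal wording of Sample size. The figures can be reconciled if four per month is a minimum and all enrolment falls in the first year. The article says neither, so the reader cannot tell what meeting the recruitment criterion would show about the feasibility of the plan. The arithmetic is certain; the authors' intention is not.

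**What to change.** State one accrual duration and one target, and use them in Outcomes, Study visits and Sample size alike. In Sample size, replace the reference to the two-year study period with the accrual period that is meant. Then choose one of the following.

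1. Keep 64 patients and 12 months of accrual, and set the criterion to the implied rate of 64/12, about 5.3 per month.
2. Keep 64 patients and four per month, and restate accrual as 16 months and the total duration as about 28 months.
3. Keep 64 patients, 12 months and four per month, and state that four per month is a deliberate minimum equal to 75% of the target rate, with the reason.

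In each case, calculate the average over the months open to recruitment. If the criterion was meant for inpatients only, say so and give the outpatient figure separately.

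The cost is a few lines of protocol wording. Option 1 makes the criterion stricter, option 2 admits a timeline four months longer, and option 3 concedes that the criterion can be met with a quarter of the target missing. Since recruitment is under way, the change should be dated and made before recruitment is judged against the criterion. The Dissemination section already provides for notifying the relevant parties of changes to outcomes.

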**Methods/design:**

Adult COPD patients at The Ottawa Hospital (TOH) will be recruited to partake in a randomized double-blind, parallel, two-arm, placebo control trial. Eligible patients will be administered either IVIG or normal saline following 1:1 randomization and every 4 weeks for 1 year. The primary outcome of feasibility will be determined by recruitment, patient adherence, safety and tolerance, success of the follow-up procedures, and outcome measurement. The safety and tolerability will be assessed through adverse events, adherence, and study withdrawals. Efficacy trends will be investigated by assessing incidence rates of AECOPD, improvement in quality of life, and healthcare services use and cost.

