### Data collection, management, and analysis

All data management and statistical analyses will be performed by the Ottawa Methods Centre at the OHRI. Study personnel will collect and enter the data on electronic case report forms, SQGR, EQ-5D-5L questionnaires, and patient cost questionnaire designed to suit this study. Case report forms will be entered into a secure database, which will be password protected and stored behind the research institution’s secure firewall. All personal health information will be kept confidential, unless release is required by law.

We will use descriptive statistics including number and proportion, means standard deviations (± SD), and medians (interquartile range) to describe the baseline characteristics of our study cohort. Descriptive analysis of recruitment, adherence, and retention of participants will also be performed in order to use this information to make changes in the definitive clinical trial.

Adverse events and tolerability will be summarized using point estimates with 95% CI for the intervention and control groups. All statistical analysis will be performed using SAS 9.3 by SAS Institute Inc., Cary, NC, USA.

Since this study is not powered to evaluate the efficacy, the changes in FEV1 value, the SGRQ and EQ-5D-5L scores, and the health service utilization will be described but not comparatively analyzed by the group as a primary outcome. AECOPD rates will be calculated on a per person/per year basis and described. To inform sample size calculations, we will use the following data obtained from this study: (1) percentage of patients with at least one recurrent AECOPD in 1 year, (2) time to first recurrent AECOPD and first recurrent hospitalization due to AECOPD, and (3) 1-year incidence of AECOPD overall and in intervention and control groups.

Routine quality control will be completed by the qualified investigator or designee at the CIU to ensure that the study is being run according to the protocol. A Data Safety Monitoring Board (DSMB) will also be appointed to assure that all participants are not exposed to unnecessary or unreasonable risks and that the study is being conducted to the highest scientific and ethical standards. DSMB meeting will occur every 6 months until the study closure. The study will be terminated if necessary for the safety of participants upon DSMB recommendation.

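### Tolerability is fixed as a completion proportion that does not separate intolerance from other reasons for stopping, so the figure mixes tolerance with persistence

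*Protocol article*

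**What the plan says.** Outcomes lists tolerability as a secondary outcome and gives it one operational definition: "The proportion of patients able to complete the treatment in the experimental arm during the study period versus in the control arm". Neither a cause of stopping nor death is mentioned.

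Interventions describes how participation can end. On the participant's side: "Participants may withdraw from the study at any time and for any reason". On the side of the sponsor, investigator or treating physician, withdrawal may be "at their discretion or in the event of intercurrent illness, intolerance to the study treatment, adverse events, pregnancy, protocol violation, or administrative reasons". Intolerance and adverse events are thus named as two reasons among several.

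The safety entry, next to tolerability in Outcomes, already collects attribution: "All adverse events will be graded by the investigator using a 5-point scale (Table 1) and scored as to attributability to study treatment". The analysis section then states: "Adverse events and tolerability will be summarized using point estimates with 95% CI for the intervention and control groups". The Abstract describes the two topics together: "The safety and tolerability will be assessed through adverse events, adherence, and study withdrawals".

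**The concern.** A tolerability measure should answer whether patients could tolerate the infusions. A completion proportion answers how many stayed on them, which also depends on illness, death, choice and administration. The protocol itself treats these as different things when it lists withdrawal reasons, but the outcome definition does not carry the distinction over.

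In this trial the other reasons need not balance between arms. The hypothesis is that IVIG reduces exacerbations, and the Background links exacerbations to admission and death. If the hypothesis is even partly right, illness-related stopping would be expected to be lower on IVIG. That raises completion on IVIG for a reason unrelated to tolerance, and so works against seeing an excess of intolerance. If IVIG has no such effect, stops for other causes still dilute the comparison.

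What is at stake is one of the trial's stated aims, to learn whether the treatment is tolerable. The figure carrying that label would be read as the answer when a larger trial is planned.

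**Working it through.** The document states no figure for tolerability and no discontinuation rate, so there is nothing of the plan's own to reproduce here. Its only calculated sample size (59 per arm) concerns exacerbations and does not enter this point.

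**Step 1: the texts side by side.**

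| Reason for ending treatment (Interventions) | A matter of tolerance? | Separated in the tolerability definition (Outcomes)? |
|---|---|---|
| Intolerance to study treatment | Yes | No |
| Adverse events | If treatment-related | No |
| Intercurrent illness | Not in itself | No |
| Pregnancy, protocol violation, administrative | No | No |
| Discretion of sponsor or physician; participant's choice | Depends on the reason | No |
| Death (not in the list) | Not in itself | No |

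**Step 2: can other-cause stopping offset intolerance?** Let *t* be the risk of stopping for intolerance and *o* the risk of stopping for anything else. Assuming the two are independent,

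completion = (1 - *t*)(1 - *o*).

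All rates below are assumptions. Take *t* = 15% on IVIG and 5% on saline, a true disadvantage of 10 points.

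| *o*, IVIG vs saline | Completion, IVIG | Completion, saline | Difference |
|---|---|---|---|
| 20% vs 20% | 0.85 × 0.80 = 68.0% | 0.95 × 0.80 = 76.0% | -8.0 |
| 10% vs 20% | 0.85 × 0.90 = 76.5% | 0.95 × 0.80 = 76.0% | +0.5 |
| 15% vs 25% | 0.85 × 0.85 = 72.25% | 0.95 × 0.75 = 71.25% | +1.0 |
| 10% vs 30% | 0.85 × 0.90 = 76.5% | 0.95 × 0.70 = 66.5% | +10.0 |

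Over the same four other-cause scenarios and one more (5% vs 15%), intolerance of 10% vs 3% gives differences from -5.6 to +13.1 points, and 20% vs 5% gives -12.0 to +5.5.

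**Step 3: the break-even.** Completion is equal when *o* on IVIG = 1 - (1 - *t* saline)(1 - *o* saline)/(1 - *t* IVIG). With 15% vs 5% intolerance and *o* = 20% on saline, this is 1 - 0.95 × 0.80/0.85 = 10.6%, so a fall of 9.4 points in other-cause stopping hides the whole 10-point excess. For *o* on saline between 15% and 30%, the fall needed is 10.0 down to 8.2 points.

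**Step 4: would a cause-specific proportion behave better?** A patient who stops first for another reason cannot later be counted as stopping for intolerance, so this proportion is also slightly affected. With constant hazards, the observed proportion is [1 - (1 - *t*)(1 - *o*)] × ln(1 - *t*)/[ln(1 - *t*) + ln(1 - *o*)]. The four rows of Step 2 give:

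- 13.5% vs 4.5%, difference 9.0 points;
- 14.3% vs 4.5%, difference 9.8;
- 13.9% vs 4.4%, difference 9.5;
- 14.3% vs 4.2%, difference 10.0 (14.26% vs 4.21% before rounding).

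It stays at 9 to 10 points against IVIG, while the completion difference moves from -8 to +10.

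**Step 5: precision.** Sample size says "we will aim to recruit 16 outpatients and 48 inpatients", that is 64, or about 32 per arm at 1:1. The 95% half-width for a difference in completion is 1.96 × √(2*p*(1 - *p*)/32): 22.5 points at *p* = 0.70, 19.6 at 0.80 and 14.7 at 0.90. For the cause-specific measure at 15% vs 5% it is 1.96 × √((0.15 × 0.85 + 0.05 × 0.95)/32) = 14.5 points. Neither measure would establish a 10-point difference in a trial of this size.

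**The case against.** The strongest reply is that the completion proportion is not read alone. Every adverse event is graded and scored for attribution by an investigator who is to be blinded, and adverse events are summarised by arm with confidence intervals. A reader might infer that a real excess of intolerance would disappear from the trial. It would not; only this one proportion could be offset. That part of the reply stands.

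A reader might also infer that the plan counts every death, discretionary stop or administrative stop as intolerance. The text does not say so. It speaks of patients *able* to complete, which could be read as leaving out a sponsor's administrative withdrawal. The supportable criticism is that causes are not separated and the wording does not settle which stops count.

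The Abstract might be taken to contradict Outcomes. It does not: it summarises safety and tolerability jointly and more broadly, and its three elements fit the detailed plan.

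The illustration rests on chosen rates, and the offset needs IVIG to lower other-cause stopping. The Background says that the association evidence does not show whether treatment helps, and nothing in the document says that an exacerbation ends infusions. This stands too: the mechanism is real, but its size in this trial cannot be stated. Any such bias may also be smaller than the sampling error. Imprecision does not cure it, however, since the interval would be centred on a quantity other than the one named.

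Finally, how deaths are counted and a table of stops by reason may be in the full protocol or analysis plan. Their absence from the article is not the point. The point is that the article does state a definition, and that definition measures something else.

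**Conclusion.** The point holds in a limited form. Tolerability is fixed as a completion proportion that merges stops for intolerance with stops for other reasons and with death, so the reported estimate and its interval describe a mixture of tolerance and persistence. If IVIG lowers illness-related stopping, completion could partly or wholly offset a real excess of intolerance. In the illustration, a fall of about 8 to 10 points in other-cause stopping is enough to cancel a 10-point excess.

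That size rests wholly on assumed stopping rates and on independence of the causes. The outcome is secondary and descriptive, attributed adverse events are reported beside it, and none of the thresholds for recruitment, adherence and retention is attached to it. A reader might infer that the feasibility decision is compromised; the document does not support that. This is a worthwhile, inexpensive improvement to one outcome definition.

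**What to change.** In Outcomes, define tolerability as the proportion of treated patients in each arm who permanently stop infusions because of an adverse event that the blinded investigator scores as related or possibly related to study treatment, or because of stated intolerance. Keep all-cause completion beside it, labelled treatment persistence, with stops tabulated by reason and deaths shown separately. Record one primary reason for stopping, entered before any unblinding.

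The Abstract needs no change, and no dosing, withdrawal or stopping rule is affected.

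The cost is a change of wording and one data field at most; attribution is already scored and no visit is added. The downside is that attribution takes judgement, and recognisable infusion reactions may suggest the allocation to the investigator. That is the reason for keeping all-cause completion alongside.
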